**3. Materials and Methods**

Participants

Fifty young adults of both sexes, aged between 18-35 years will be recruited through wide dissemination on the campus of the Federal University of Rio Grande do Norte-UFRN. The sample size was determined with G * Power of the F test family (RM-ANOVA with intra-between interaction), considering a moderate to high effect size (f = 0.3) at α = 0.05 and 80% of power, as well as 60% correlation between repeated measures and considering loss of participants during the study being necessary at least 40 participants to attend these parameters.

Participants will be interviewed in advance and will complete a series of questionnaires to verify their eligibility for the study. Upon being elected to the study, they will be randomized into two groups proposed in this study.

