**Amsterdam Resting-state Questionnaire- ARSQ**

This instrument aims to assess the relationship with thoughts in a state of rest. Developed by Diaz et al., 2013 and improved in 2014 (ALEXANDER DIAZ et al., 2014; DIAZ et al., 2013), it seems to be of great value when applied to participants undergoing contemplative practices. Version 2.0 to be used in this study consists of 54 items that should be answered on a scale of 1-5 that varies from “completely disagree” to “completely agree”.

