**Statistical analysis**

Initially, Kolgomorov-Smirnov normality tests will be applied to determine if the data obey a normal distribution. Once this prerequisite is met, Student's t test (parametric variables) or Mann Whitney U test (non-parametric variables) will be applied to detect the occurrence of significant differences within group and ANOVA to evaluate between groups differences. Spearman's correlation test will also be applied to test the occurrence of correlations between variables (anxiety, affect, stress and mindfulness, trait and state).

An exploratory and confirmatory factor analysis will be performed to verify the domains and association between the factors existing in the questionnaires. The internal consistency of the factors will be verified using Crombach's Alpha and only saturation values ​​greater than 0.4 for the eigenvalues ​​will be computed for the item's participation in the investigated domain.

For the analysis of plasmatic and behavioral markers, correlation tests and multivariate analysis will be used.

For all tests, the significance level (p value) less than or equal to 0.05 will be considered.

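### With at most 50 participants, the planned exploratory and confirmatory factor analysis cannot verify the domains of the longer questionnaires, and its 0.4 item rule is worded for the wrong quantity

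*Protocol*

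**What the plan says.** The Statistical analysis section commits to both kinds of factor analysis: "An exploratory and confirmatory factor analysis will be performed to verify the domains and association between the factors existing in the questionnaires". It does not list the scales, name an extraction method or number of factors, or describe a separate or split sample. It then sets a threshold of 0.4. The threshold uses the term saturation, which means a loading, but is attached to eigenvalues. Only values above it "will be computed for the item's participation in the investigated domain".

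The only sample in the protocol is under 3. Materials and Methods: "Fifty young adults of both sexes, aged between 18-35 years will be recruited". It was sized for "RM-ANOVA with intra-between interaction", with "being necessary at least 40 participants to attend these parameters". No sample size is given for the factor analysis.

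Item counts appear in the questionnaire sections: MAAS 15, PANAS 20 (two scales of 10), STAI two parts of 20, SMS 21, MAIA 32, FFMQ 39. For the ARSQ: "Version 2.0 to be used in this study consists of 54 items". No count is given for the short Perceived Stress Scale. The sections on the MAIA, MAAS and SMS say that the team will work on validating those instruments. The Questionnaires section has the scales given before, during and after the interventions.

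**The concern.** Factor analysis estimates a structure from the correlations among items, so it needs many more people than items. Here the longest scale has more items than the trial has people, and the next two have nearly as many. An analysis of that size cannot verify domains, which is its stated purpose.

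The item rule adds a second problem. Eigenvalues belong to factors, not to items, so a cut-off on eigenvalues cannot decide whether an item belongs to a domain. Read as a cut-off on loadings, it would be applied to very imprecise estimates.

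Under 2. Objectives, several aims are measured by these questionnaires (self-reported stress, anxiety, affect, trait mindfulness, interoception). If the rule were used to choose the items scored in the arm comparison, the outcomes would be built from item sets picked in the same data. They would be unstable, open to analytic choice and not comparable with the published instruments. The protocol allows that use but does not state it.

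**Working it through.** **1. The plan's own sample-size figure.** The inputs, from 3. Materials and Methods, are "moderate to high effect size (f = 0.3) at α = 0.05 and 80% of power" and "60% correlation between repeated measures". The number of measurements m is not stated. I used the G*Power default for the within-between interaction with two groups: λ = f²·N·m/(1 − ρ), with degrees of freedom m − 1 and (N − 2)(m − 1).

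- For m = 2 and N = 20: λ = 0.09 × 20 × 2 / 0.4 = 9, and power is 81%. So N = 20 is enough.
- For m = 3, 4 and 5 the required N is 16, 14 and 12.
- At N = 40 and m = 2, power is 98.5%.

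The stated 40 is not reproduced, but it exceeds what its inputs require, and nothing below depends on it. What matters is that the sample was sized for a repeated-measures ANOVA and not for factor analysis.

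**2. People per item and model size at n = 50.** Free parameters of a simple-structure confirmatory model = p loadings + p residual variances + k(k − 1)/2 factor correlations, for p items and k factors.

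| Scale | Items p | People per item | Factors k | Free parameters |
|---|---|---|---|---|
| MAAS | 15 | 3.3 | 1 | 15 + 15 + 0 = 30 |
| PANAS | 20 | 2.5 | 2 | 20 + 20 + 1 = 41 |
| SMS | 21 | 2.4 | 2 (assumed) | 21 + 21 + 1 = 43 |
| MAIA | 32 | 1.6 | 5 | 32 + 32 + 10 = 74 |
| FFMQ | 39 | 1.3 | 5 | 39 + 39 + 10 = 88 |
| ARSQ | 54 | 0.93 | 10 (assumed) | 54 + 54 + 45 = 153 |

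The factor counts for the MAAS, PANAS, MAIA and FFMQ follow the protocol's descriptions. Parameters outnumber people for the MAIA, FFMQ and ARSQ, but not for the MAAS, PANAS or SMS.

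**3. Rank of the covariance matrix.** The rank is at most min(p, n − 1).

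- ARSQ at n = 50: at most 49 of 54. The matrix is singular, its log-determinant does not exist, and neither does the maximum-likelihood fit or its chi-square. Full rank would need at least 55 people, which is a minimum for the fit to exist and not an adequate sample size.
- At n = 40: rank at most 39. The FFMQ (39 items) is only just full rank and becomes singular with 39 or fewer people.
- If the sample is split 25/25 so that the confirmatory step is independent of the exploratory one: rank at most 24. The MAIA, FFMQ and ARSQ are then all singular.
- Pooling the repeated administrations adds correlated rows, not people.

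**4. Precision at the 0.4 cut-off.** Fisher's z for a correlation of 0.4 is 0.424, with half-width 1.96/√(n − 3).

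- n = 50: 0.424 ± 0.286, giving 0.14 to 0.61.
- n = 40: 0.424 ± 0.322, giving 0.10 to 0.63.

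**5. Behaviour of the rule in simulation** (normal items, varimax rotation, n = 50, 80 to 150 runs per setting).

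- *All items unrelated, number of factors fixed.* Share of items passing 0.4: with one factor, 29–35% for principal components and 16% for principal axis; with 2 to 10 factors, 49–79% and 26–56%.
- *Real simple structure, principal axis.* With true loadings of 0.5, the share of retained loadings that are true is 99–100% for 15–20 items, 86–89% for 32–39 items and 68% for 54 items. At 0.6 it is 89–100%, and at 0.7 it is 98–100%. The rule misses 20–47% of true loadings of 0.5.
- *Mixed scales.* If half the items are noise, noise makes up 1–47% of the items kept. If 20% are noise, it makes up 0–18%.

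**The case against.** **The rule keeps mostly noise?** A reader might infer this from the 49–79% pass rates. They do not support it. They are the share of unrelated items that pass when every item is unrelated and principal components are used; they are not the share of retained items that are noise. Published scales are not sets of unrelated items: the protocol gives the MAIA an internal consistency of 0.82. In no simulated setting with real structure was most of what was kept noise.

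**The analysis cannot be computed?** Only under conditions. It requires maximum likelihood, and it requires the ARSQ to be among the scales factored. The protocol names no estimator. It states validation intent only for the MAIA, MAAS and SMS, all below 40 items, although the wording about the questionnaires includes the ARSQ on a plain reading. Principal-axis or least-squares extraction would still run on a singular matrix. For the MAIA and FFMQ, more parameters than people signals instability, not impossibility. The models are over-identified, with 528 − 74 = 454 and 780 − 88 = 692 degrees of freedom.

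**The outcome scores will be redefined?** This too might be inferred, but it is not a stated plan. The purpose given is to verify domains, which can be read as psychometric checking, and the wording about an item's participation is ambiguous. Elsewhere the protocol points to established scoring: STAI totals of 20 to 80, all MAAS items measuring one construct, and validated versions of the PSS and PANAS.

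**Is this detail for the SAP?** Extraction method and scale list may well be. The commitment to both analyses, the misworded 0.4 rule and the size of the only sample are fixed in the protocol. That part of the concern stands.

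**Conclusion.** The concern holds in a limited form. With at most 50 people, the planned factor analysis cannot verify the domains of the MAIA (74 parameters) or FFMQ (88). If the ARSQ is included, its covariance matrix has rank at most 49 of 54 and no maximum-likelihood fit exists. There is no sound way to do both steps: on the same people the second is not confirmatory, and on halves of the sample the three longest scales are singular. The 0.4 rule is unusable as worded. Read as a rule on loadings, it does not reliably separate real items from noise at this size.

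The effect on trial outcomes is conditional: it arises only if the rule selects the items that are scored when the arms are compared. Cortisol, autonomic, EEG, heartbeat-counting and attention-task outcomes are unaffected. No stated objective depends on the factor analysis. Severity is minor to moderate.

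The parameter counts assume simple structure, with two SMS and ten ARSQ factors assumed. The simulations assume normal items and varimax rotation. The rank limits need none of these assumptions.

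**What to change.** Delete the exploratory and confirmatory factor analysis and the 0.4 rule from the Statistical analysis section. If the team wishes to keep some factor analysis, label it as exploratory psychometrics that changes no score, and state the cut-off in terms of item loadings.

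Add one sentence: every questionnaire is scored with all its items by its published key, fixed before the data are analysed, and the arms are compared on those scores. Report Cronbach's alpha descriptively on the day-1 data.

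This removes work and adds none. The price is that no validation claim for the Brazilian versions can come from this trial. If validation is still wanted, it needs a separate and larger sample, which is a new resource and not part of this correction.

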**2. Objectives**

General:

• Assess the impact of a brief training on the stress response, interoception and well-being on healthy individuals.

Specific:

• Verify the relationship between mindfulness trait and hypothalamic-pituitary-adrenal axis reactivity.

• Analyze the neuroendocrine response to a stress event after a brief mindfulness-based intervention.

• Assess the impact of mindfulness practice (3 days) on the attention system, autonomic nervous system, and interoceptive ability.

• Check the influence of the practice on self-report measures of stress, anxiety, and affect

• Assess participants' electroencephalographic activity before and after the proposed intervention, during a sustained attention test, an interoception test, and during the stress test.

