**Multidimensional Assessment of Interoceptive Awareness - MAIA**

Questionnaire designed to measure the ability to identify emotions and interoceptive bodily sensations (MEHLING, 2012). Items fall into some domains that refer to the following factors:

1) Awareness of bodily sensations.

2) Emotional reaction and attentional response to bodily sensations.

3) Emotion regulation capacity.

4) Consciousness of Mind-Body Integration.

5) Confidence in bodily sensations.

The instrument contains 32 items and has an internal consistency of 0.82. We will work on validating this questionnaire for the Brazilian population and using the version translated into Portuguese (MAIA-VB2).

Mindful Attention Awareness Scale (MAAS)

Scale that assesses the level of Mindfulness, consisting of 15 items, on a six-point Likert scale ranging from (1) almost always to (6) almost never. The scale is one-dimensional, so all items measure Mindfulness. We will use the Brazilian version of the questionnaire (ATANES et al., 2012) and we will work on validating this version.

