**FFMQ- Five Facets of Mindfulness Questionnaire - (FFMQ)**

This scale assesses the level of Mindfulness and is composed of 39 items on a five-point Likert scale ranging from (1) never or rarely true to (5) almost always or always true. On this scale, the concept of Mindfulness is divided into five components, they are:

(1) Observing, which includes noticing or being aware of internal and external experiences, such as sensations, cognitions, emotions, sights, sounds and smells.

(2) Describe, which refers to characterizing internal experiences through words.

(3) Acting with awareness, which refers to being aware of the activities of the moment and can be contrasted with mechanical behavior while attention is focused on something else, known as autopilot.

(4) Non-judgment of internal experience, which refers to not taking an evaluation and judgmental stance in relation to thoughts and feelings.

(5) Non-reactivity to internal experience, which refers to the tendency to allow thoughts and feelings to come and go without being affected or taken over by them (BAER et al., 2006). We will use the Brazilian version of the questionnaire (BARROS et al., 2014).

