**State Mindfulness Scale - (SMS)**

This scale aims to assess levels of mindfulness related to the state of consciousness (TANAY; BERNSTEIN, 2013). It was developed based on previous mindfulness trait scales and seeks to complement the mindfulness assessment at the time of its application. It is a scale that contains 21 items where the individual will have to answer the questions with a graduation from “nothing” to enough”. We will work on validating this scale for the Brazilian population.

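### One 0.05 threshold applies to every test and no primary outcome is named among about 28 measures, so false positives are not controlled

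*Protocol*

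**What the plan says.** The Statistical analysis section closes with a rule for the whole trial: "For all tests, the significance level (p value) less than or equal to 0.05 will be considered". Earlier it assigns t or Mann-Whitney tests "to detect the occurrence of significant differences within group and ANOVA to evaluate between groups differences", and adds that "Spearman's correlation test will also be applied to test the occurrence of correlations between variables". For plasma and behavioural markers it mentions correlational and multivariate methods without specifying them. It gives no order of importance, no adjustment and no division into confirmatory and exploratory tests.

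The general objective in section 2 is broad: "Assess the impact of a brief training on the stress response, interoception and well-being on healthy individuals". Five specific objectives follow, covering mindfulness trait and the stress axis, the neuroendocrine response to stress, attention, autonomic function and interoception, self-report, and EEG. None is ranked above the others.

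The Participants paragraph in section 3 sizes the trial for one repeated-measures ANOVA interaction (f = 0.3, alpha 0.05, power 80%, correlation 0.6, at least 40 participants needed, 50 to be recruited). It does not say which outcome that test concerns.

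**The concern.** A sample size computed for one test at 0.05 implies one confirmatory question. The analysis rule gives every measure the same standing and the same threshold. With many measures and no outcome named beforehand, some nominally significant result is likely even if three 30-minute sessions change nothing, and nothing in the protocol separates that result from a planned finding. The protocol's benefits section looks towards use in education and the public health system, so a chance result presented as support would matter.

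**Working it through.** **The plan's own figure.** The protocol states no family-wise error rate. Its one computed figure on this point is the minimum of 40 participants. For a two-group interaction with m measurements, lambda = N f² m / (1 − rho), with m − 1 and (N − 2)(m − 1) degrees of freedom. With f = 0.3, rho = 0.6, alpha 0.05 and power 80%, the required N before loss is 20 (m = 2), 16 (m = 3) or 14 (m = 4). The protocol gives neither m nor a loss rate, so 40 can be neither reproduced nor refuted, and nothing below depends on it. What matters is that the calculation covers a single test.

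**Counting the measures.** Each named measure is counted once:

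- Salivary cortisol 1 (sampled four times around the stress test), blood cortisol 1, BDNF 1: 3
- Heart rate variability, four named frequency measures: 4 (running total 7)
- Heartbeat-counting accuracy: 1 (8)
- Sustained attention, correct answers and response time: 2 (10)
- MAIA, five listed domains ("Items fall into some domains that refer to the following factors"): 5 (15)
- MAAS ("The scale is one-dimensional, so all items measure Mindfulness"): 1 (16)
- FFMQ ("the concept of Mindfulness is divided into five components"): 5 (21)
- SMS ("It is a scale that contains 21 items"): 1 (22)
- Perceived stress 1, PANAS 2, ARSQ at least 1, STAI 2: 6 (28)

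EEG, skin response, time-domain heart rate variability, blood profiles and correlations are not in this count.

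**Independent statistics, no true effects, one between-group test each.**

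- Chance of at least one p ≤ 0.05: 1 − 0.95^28 = 0.762.
- Expected number of false positives: 28 × 0.05 = 1.4. This holds under any correlation.
- One half is passed at 14 tests: 1 − 0.95^14 = 0.512, against 1 − 0.95^13 = 0.487.

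**The same correlation rho between all 28 statistics.** With c = 1.96 and z standard normal, the chance is 1 − E{[Φ((c − √rho·z)/√(1 − rho)) − Φ((−c − √rho·z)/√(1 − rho))]^28}.

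| rho | chance of at least one |
|---|---|
| 0.1 | 0.743 |
| 0.3 | 0.641 |
| 0.4 | 0.570 |
| 0.5 | 0.491 |

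The value crosses one half at rho of about 0.49.

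**Correlation only within families.** The assumed families are MAIA 5; MAAS, FFMQ and SMS 7; perceived stress, PANAS and STAI 5; ARSQ 1; endocrine 3; heart rate variability 4; heartbeat accuracy 1; attention 2 (total 28).

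| rho within family | chance of at least one |
|---|---|
| 0.3 | 0.734 |
| 0.5 | 0.688 |
| 0.7 | 0.618 |
| 0.8 | 0.569 |

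In the limit of perfect correlation within each of the eight families it would be 1 − 0.95^8 = 0.337.

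**A smaller count, under independence.**

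- Without separate tests for blood cortisol, BDNF and the two attention scores: 28 − 4 = 24, and 1 − 0.95^24 = 0.708.
- If MAAS and FFMQ also serve only as predictors: 24 − 6 = 18, and 1 − 0.95^18 = 0.603.
- If MAIA is also reduced to one score: 18 − 4 = 14, which gives 0.512.

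**After the fix.** One primary test at 0.05 has a 5% false-positive chance on the confirmatory claim. For comparison, Bonferroni over 28 tests uses 0.05/28 = 0.0018 per test, and 1 − (1 − 0.05/28)^28 = 0.049 under independence.

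**The case against.** The strongest reply is that adjustment methods, test families and the confirmatory or exploratory label are commonly left to a SAP, which may exist. The 0.05 rule could also be read as the level against which adjusted p-values will be compared. This stands in part: the absence of adjustment detail alone would not be a finding. However, the protocol itself fixes the threshold for all tests without mentioning adjustment. Choosing the primary outcome belongs in the protocol, above all when the sample size presupposes one.

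Second, 28 separate between-group tests is an inference. Plasma and behavioural markers may be handled by multivariate methods, a factor analysis of the questionnaires is planned, and the first specific objective uses mindfulness trait as a correlate of stress-axis reactivity. This also stands. The rate is therefore conditional, and a count below 14 independent tests would bring it under one half. Against that, EEG, skin response and the correlations are left out of the count.

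Two stronger readings are tempting and are not supported.

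- A reader might infer that within-group tests in both arms treble the number of tests and hence the expected false positives. Salivary cortisol is assayed from day 3 only, so it has no pre/post-training pair. Within-group change can also be a real effect of time, task practice or the stressor. Such results are poor evidence for the training, but they are not errors occurring at a 5% rate.
- A reader might infer that the trial cannot confirm any objective. No section says that a single p ≤ 0.05 makes the trial positive, and a clear result could survive adjustment.

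**Conclusion.** The concern holds as a conditional statement. The protocol states a uniform 0.05 rule, names no primary outcome among about 28 measures, and sizes the trial for one unnamed test. Followed as written, the rule does not control the chance of a false positive across the trial.

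The size is 76% under independence and about 57% to 73% with moderate to strong correlation within families, with 1.4 false positives expected in every case. These figures assume that every null hypothesis is true and that each measure receives one between-group test. The protocol gives no correlations between outcomes. A common correlation above about 0.49 across hormones, heart rate variability, reaction times and questionnaires would be needed to bring the equal-correlation figure below one half, and that seems unlikely. Near-perfect correlation within families would also do it. The point should be corrected, but it does not invalidate the design.

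**What to change.** Before any data are seen, the sponsor should name one primary outcome and one primary between-group test. That test would be group by time, or group by sample time if day-3 salivary cortisol is chosen. Salivary cortisol around the stress test is one candidate, because the stress response comes first in the general objective. The introduction gives weight to interoception and cortical activity as well, so the choice is the sponsor's. The Participants paragraph should then name that outcome, the number of measurements and the loss allowed for.

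Replace the last sentence of the Statistical analysis section with:

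> The primary test uses two-sided 0.05. Secondary between-group tests are adjusted within families (Holm or Benjamini-Hochberg). All other tests, including within-group tests and correlations, are exploratory and reported with estimates and intervals.

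EEG is a stated objective, so the sponsor should say whether its between-group comparisons form a secondary family or are exploratory.

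The cost is stricter thresholds for secondary outcomes, and a sample-size paragraph that has to be completed and rechecked against the chosen outcome. The multiplicity rule itself adds no participants, visits or assays.
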